### Protocol adherence

The EGDT algorithm is easy to use and rather straightforward, yet extensive training of nurses and physicians involved in the care of patients allocated to EGDT will be performed before the start of the study in each participating center. Moreover, a number of nurses and physicians from each institution have been involved in the trial from the beginning and are thoroughly informed about the procedures. These ‘trial experts’ can be consulted at any time and will monitor the appropriate application of the EGDT algorithm.

### Outcome measures

The primary outcome measure is the number of major complications per patient within the first 30 days after surgery, including mortality. An overview of all major complications can be found in Table 2. The complications within this composite endpoint are associated with increased long-term morbidity and mortality [3].

**Table 2 Tab2:** **Major complications within the first 30 days after surgery embedded in the composite primary endpoint**

Category	Complication	Criteria
Mortality	30-day mortality	Mortality within the first 30 days after surgery
Cardiovascular	Cardiac arrest	Cardiac arrest, electromechanical dissociation, ventricular fibrillation, or ventricular tachycardia without output
	Acute myocardial infarction	According to the criteria for acute myocardial infarction (see Universal Definition of Myocardial Infarction [27])
	Acute pulmonary edema	Diagnosis confirmed by X-ray
	Stroke	Focal brain injury that persists for >24 hours, combined with an increase in disability of at least one grade on the modified Rankin scale [28], confirmed by cerebral CT-scan
Respiratory	Prolonged mechanical ventilation	Postoperative mechanical ventilation for more than 24 hours (any cause), including non-invasive pressure support ventilation through a face-mask
	Pulmonary embolism	Confirmed by CT-scan
	Pneumonia	Confirmed by X-ray and treated with antibiotics
	Respiratory failure	Any other respiratory complication requiring mechanical ventilation (including non-invasive pressure support ventilation)
Renal	Acute kidney injury	Stage 2 or 3 acute kidney injury, according to the Acute Kidney Injury Network [29]
Gastrointestinal	Anastomotic leak	Diagnose made and confirmed by surgeon
	Other	Any other complication requiring additional surgery
Infection	Wound	Diagnosis made and confirmed by surgeon
	Severe sepsis	See International Sepsis Definitions Conference [30]

The following secondary outcome measures are considered: the grade of major complications occurring in the first 30 days after surgery according to the Accordion Severity Grading system [31]; the number of the following minor complications within the first 30 days after surgery: arrhythmia (requiring intervention), deep venous thrombosis (confirmed by ultrasonography), urinary tract infection (confirmed by urinalysis and treated with antibiotics), prolonged ileus (diagnose made and confirmed by surgeon), herniation or other prolonged wound healing (diagnosis made and confirmed by surgeon); the total amount of fluid administered in the first 24 hours after surgery (crystalloids, colloids, and blood products); inotropic support in the first 24 hours after surgery (amount and duration of infusion); hemodynamic (blood pressure, HR, CI, SVV, mean urine output) and laboratory (central venous oxygen saturation and pCO_2_, serum lactate, troponin) variables in the first 24 hours after surgery; length of stay in the hospital and in the ICU/PACU; continuation of care at intermediate care units (level of care in between the ward and ICU/PACU); number and length of ICU/PACU or intermediate care readmissions; QOL; cost-effectiveness; long-term outcome: 3, 6, and 12 months complications and mortality.

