### Previous literature

Before the start of the study we performed a systematic review of the literature to evaluate all available evidence on the use of EGDT in elective, high-risk, abdominal surgery (Additional file 1). The results indicated that EGDT is a promising strategy to reduce morbidity and even mortality in high-risk surgery. There are, however, several limitations to the previous literature which may explain why EGDT has never been widely implemented into routine practice [19]. First, the results from most studies are outdated and not applicable to the current standard of care. In studies from 1988 to 2000, morbidity and mortality are much higher in comparison with current practice, even in the intervention groups. The same applies for length of stay in the hospital. Second, pulmonary artery catheterization has been used for the purposes of EGDT at that time. As described before, this technique is limited to specific types of surgery and not broadly accepted for perioperative monitoring in non-cardiac surgery [11–13, 20]. Two studies applying arterial waveform analysis for EGDT purposes were small and performed in a single center [4, 6]. Moreover, minor complications, such as short-lasting intraoperative hypotension or urinary tract infection, are included as an outcome measure. These complications are not associated with increased long-term morbidity and mortality and should be evaluated separately. One final but major limitation applies to all of the studies described. They lack information about the effect of EGDT on long-term outcome, quality of life, and utilization of healthcare resources. This hinders a cost-effectiveness analysis. EGDT requires the purchase of CO monitoring equipment which consists of specific patient monitors and arterial blood pressure sensors. Additional costs may be the result of an increased use of inotropic support or other therapeutic consequences of EGDT.

Since the start of the trial in May 2012, a number of interesting studies have been published which partially addressed the shortcomings mentioned above [5, 21–23]. Two studies demonstrated that the implementation of a goal-directed strategy was cost-effective [21, 22]. In addition, two multicenter studies were performed in which a reduction in complications was shown [5, 23]. However, minor complications were included, and the number of patients was rather small in these studies.

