## Methods/Design

### Trial design

The EGDT trial is designed as a multicenter, randomized, controlled superiority trial with two parallel groups in a 1:1 allocation. The trial is unblinded for the clinicians involved, the patients, and the observers.

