#### Blinding

Ideally, blinding is used at the level of the patient, the caregiver, and the assessor of the outcome variable. In our trial however, blinding at the patient and caregiver is simply impossible. In theory, it is possible to use blinded assessors to determine outcome measures according to specified criteria. However, patient follow-up should be active and thorough, in order not to overlook complications and adverse outcomes once the patient is in the ward or at home. This requires frequent visits to the patients and monitoring of the patients’ medical records. During these visits and in these records, information about the use of CO monitoring and PLR testing is easily obtained, which makes blinding impossible. Therefore, all variables are elaborately defined, especially outcome parameters. Strict criteria are used to define the complications embedded in the composite primary endpoint. In this way, we aim to minimize bias as much as possible.

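### Two components of the unblinded primary count, anastomotic leak and wound infection, rest on the surgeon's diagnosis alone; pre-specified sensitivity analyses would be a cheap improvement

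*Protocol article*

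**What the plan says.** Under Trial design: "The trial is unblinded for the clinicians involved, the patients, and the observers". The Blinding section explains why blinded outcome assessors were judged unworkable and then names the substitute: "Strict criteria are used to define the complications embedded in the composite primary endpoint". It adds: "In this way, we aim to minimize bias as much as possible".

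Table 2 lists the components. Most carry a test, a stage, a duration, a treatment or a published definition. Pneumonia reads "Confirmed by X-ray and treated with antibiotics"; kidney injury reads "Stage 2 or 3 acute kidney injury, according to the Acute Kidney Injury Network". Two rows differ. Wound infection reads "Diagnosis made and confirmed by surgeon" and anastomotic leak reads "Diagnose made and confirmed by surgeon".

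In Outcome measures, the minor complications prolonged ileus and herniation or other delayed wound healing are defined by the same surgeon-confirmation formula. The minor urinary tract infection must be shown on urinalysis and treated with antibiotics, and the minor deep venous thrombosis must be shown on ultrasonography.

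Two provisions bear on the point. The Primary endpoint section promises to report every complication separately and to weigh complications by Accordion severity, and the Accordion grade of major complications is a secondary outcome.

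**The concern.** The strict criteria are the protection the article offers in place of blinded assessment, so they need to hold for each item that adds to the count. For leak and wound infection, the criterion is a clinician's judgment, and that clinician may know the allocation. For wound infection nothing sets a minimum severity, so the label chosen decides whether a wound problem adds one to the primary count or goes to the minor list.

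If the label were applied more readily in one arm, the difference would pass straight into the rate ratio for major complications. The analysis as described could not separate it from a treatment effect.

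**Working it through.** **1. Setting the rows side by side.**

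| Item | Class | What must be shown |
|---|---|---|
| Pneumonia | major | X-ray and antibiotics |
| Pulmonary embolism | major | CT |
| Acute kidney injury | major | stage 2 or 3 |
| Anastomotic leak | major | surgeon's diagnosis |
| Wound infection | major | surgeon's diagnosis |
| Delayed wound healing | minor | surgeon's diagnosis |
| Urinary tract infection | minor | urinalysis and antibiotics |

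The two major items in question meet a looser standard than a minor infection does, and the same standard as a minor wound problem.

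**2. The plan's own figure.** Inputs from Statistical analysis and sample size calculation: control rate 0.58 per patient, 30% reduction (RR 0.70), two-sided 5%, power 80%. Signorini's Poisson-regression formula gives

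N = [1.96·√4 + 0.8416·√(2 + 2/0.70)]² / [0.58·(ln 0.70)²] = 452, or 226 per group.

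226 × 1.2 = 271.2. The stated 226, 271 and 542 all reproduce. The concern does not touch this calculation.

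**3. How much labelling could matter (illustration).** The share *s* of the 0.58 events that are leaks or wound infections is not given; take 10–40%. Suppose no true effect, and suppose a fraction *u* = 10–30% of these items goes unrecorded in the intervention arm. Both ranges are assumptions. Then

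- apparent RR = 1 − *s·u*
- expected control events = 271 × 0.58 = 157.2
- SE(ln RR) = √[1/157.2 + 1/(157.2·RR)]
- d = −ln(RR)/SE
- two-sided rejection = Φ(d − 1.96) + Φ(−d − 1.96)

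| *s* | *u* | RR | d | rejection |
|---|---|---|---|---|
| 10% | 10% | 0.99 | 0.09 | 5.1% |
| 20% | 20% | 0.96 | 0.36 | 6.5% |
| 30% | 20% | 0.94 | 0.54 | 8.4% |
| 30% | 30% | 0.91 | 0.82 | 12.9% |
| 40% | 30% | 0.88 | 1.10 | 19.5% |

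**4. What dropping the two items costs in precision.** With 271 per arm, a true RR of 0.70 on all components and a Wald test on the log rate, power = Φ(0.3567/SE − 1.96), with SE = √[1/a + 1/(0.7a)] and a = 157.2·(1 − *s*). All components: a = 157.2, SE 0.124, power 82%. Without the two items: *s* = 10%, a = 141.5, 78%; *s* = 30%, a = 110.0, 67%; *s* = 40%, a = 94.3, 60%.

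**5. What redefining the primary count would cost.** Assume a 30% share and that half of those events cease to count: 0.58 × (1 − 0.15) = 0.493. The formula in step 2 then needs 266 per group, and 266 × 1.2 = 319, against 271 planned.

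**The case against.** Several counter-arguments have weight.

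- *Severity is not ignored.* Accordion grading is planned, and the article explains why a severity-weighted primary endpoint was rejected. That stands: equal weighting is a disclosed choice. But the grade does not decide what enters the primary count, and separate reporting shows where a difference lies without showing whether it is real.
- *Wound infection is not called minor.* A reader might infer that the article condemns its own endpoint where it says of minor complications in earlier trials: "These complications are not associated with increased long-term morbidity and mortality and should be evaluated separately". Its examples there are brief intraoperative hypotension and urinary tract infection. Wound infection is not named, and delayed wound healing is a separate item, so that inference is not supported.
- *Fuller definitions may exist.* The article calls Table 2 an overview, and a full protocol or case report form may say more. This is possible. But the table prints criteria, the Blinding section relies on them, and none of the additional files is cited for endpoint definitions.
- *The surgeon's knowledge of allocation is inferred.* It follows from the unblinding of the clinicians involved and from the statement that caregivers cannot be blinded. The article does not say that the confirming surgeon takes part in the algorithm or knows the arm at that moment.
- *Tighter criteria are not bias-free.* Giving antibiotics, opening a wound, ordering imaging and reoperating are also decisions of unblinded clinicians, as are other Table 2 items such as complications needing further surgery. That stands, and it limits what any fix can achieve.
- *Sensitivity analyses belong in the analysis plan.* Agreed; their absence from the article is not the fault. The fault is the mismatch between the claimed safeguard and two rows of the table.

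**Conclusion.** The point holds as a cheap improvement. The stated safeguard does not cover anastomotic leak and wound infection, so the primary count is open to differential labelling on those two items.

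The size is unknown. On the assumed ranges the apparent rate ratio lies between 0.99 and 0.88 and the two-sided error between about 5% and 19.5%. The low end is of no consequence; the high end needs both a large share and substantial under-recording.

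A reader might infer that the trial is biased in favour of goal-directed therapy, or fix on one cell such as the 8.4%. The documents support neither: they give no component shares and no evidence of under-recording, and the direction in the table is assumed. Nor do they show that the primary endpoint must be rewritten. About 160 patients were already enrolled by the end of 2013, and a mid-trial redefinition in an open-label study brings its own risk of bias and a loss of power.

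**What to change.** Keep the primary count as defined. Before any comparison by arm, pre-specify:

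1. a sensitivity analysis that counts a leak only if documented by imaging, endoscopy or reoperation, and a wound infection only if documented with antibiotic treatment or wound opening or drainage, applied identically to all patients from the records;
2. a sensitivity analysis of the count without these two components;
3. a statement that a claim of fewer major complications is qualified if it does not persist in these analyses. Given the power in step 4, judge persistence by the rate ratio and its confidence interval, not by whether P stays below 0.05.

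Much of the evidence is already gathered: Data collection takes cultures, imaging, reoperation, drainage and antibiotic treatment from the medical records for the cost analysis. Endoscopy and wound opening are not named there and may need extra abstraction.

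If the sponsor prefers to amend Table 2, the same record-based criteria should apply to every patient, without reference to results by arm, and the power should be restated for the lower event rate (step 5 shows the possible scale).

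Cost: some extra abstraction, no new staff or procedures, and fewer events and lower precision in the sensitivity analyses. The criteria reduce the bias rather than remove it.

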### Data collection

Before the operation demographic data, ASA physical status, medical history, and drug usage are collected from the patient’s medical records.

A number of hemodynamic variables (blood pressure, HR, CI, and SVV if applicable) are recorded each hour during the first 24 hours after induction. In the EGDT group, these variables are also recorded before and after interventions to correct a drop in CI below the target value. Fluid balance in the first 24 hours is evaluated by recording the amount of fluids infused (crystalloid, colloid, and blood products) as well as urine output and blood loss. In addition, the use of inotropes is registered (type, amount, and duration of infusion). The following laboratory variables are determined after induction, during surgical closure, after admittance to the ICU/PACU, and the morning after surgery: serum hemoglobin, lactate, and full blood gas analysis (arterial and venous). After admittance to the ICU/PACU, the following additional blood values are determined in order to calculate the Sequential Organ Failure Assessment (SOFA) score [32]: serum creatinine, bilirubin, and platelet count. The morning after surgery, serum troponin and creatinine levels are measured. The Therapeutic Intervention Scoring System (TISS) is calculated after admittance to the ICU/PACU [33]. Variables are derived from the patient monitoring systems used in the operating room and ICU/PACU, or from the OR and ICU/PACU record systems.

The following information is obtained in the first 30 days after surgery: all-cause mortality, major and minor complications, if applicable; duration of postoperative mechanical ventilation (hours); length of stay in the in the hospital (days) and ICU/PACU (hours); length of stay in the in the hospital (days) and ICU/PACU (hours) according to fit-for-discharge criteria [5] (Additional file 3); continuation of care at intermediate care units (hours); number of readmissions to the ICU/PACU or intermediate care unit.

All information can be obtained from the patients’ medical records. Patient follow-up with respect to complications and length of stay is active.

QOL will be assessed with the EQ-5D and Short Form (SF) 36 questionnaires before surgery and 1, 3, 6, and 12 months after surgery. Depending on the patient’s preference, the questionnaires are sent to the patient by email or conventional mail, or the patient is called by an interviewer. Patients who do not respond will receive a maximum of two phone calls as a reminder. Before contacting or sending the questionnaires to the patient, confirmation will be obtained that the patient is still alive.

Both healthcare costs (treatment costs including equipment, hospital stay, and re-interventions) and non-healthcare costs (costs as a result of absence from work) will be analyzed. Additional equipment and staff costs associated with EGDT will be monitored to assess incremental costs associated with EGDT. Direct healthcare costs will be calculated by multiplying the volume of (healthcare) resources use with its cost, using standard reference prices for economic evaluation in healthcare whenever available. Information on the following direct costs will be collected from the medical records: blood sample measurements, cultures and other investigations (such as chest films, CT-scans, echography, and ECG), interventions (such as reoperation, catheterization, chest drainage, and antibiotic treatment), and discharge destination (home, nursing home, rehabilitation). Data on absenteeism from work will be collected using parts of the Short-Form Health and Labor Questionnaire (SF-HLQ). The following three questions are added to the SF-HLQ: how many times did you visit your general practitioner? How many times did you visit a doctor in the hospital? Have you been admitted to the hospital? These questions are included in the QOL questionnaire described above. Indirect costs associated with production losses will be estimated using the friction cost method.

Long-term outcome is determined with a letter to the general practitioner of the patient after 3, 6, and 12 months. In this way, mortality and morbidity in the period between 30 days and one year after the operation is determined.

### Statistical analysis and sample size calculation

A study of the hospital data of one of the participating centers revealed that the number of major complications embedded in the composite primary endpoint was 0.58 per patient, and that a Poisson distribution was applicable. We aim to reduce the number of major complications per patient by 30% (from 0.58 to 0.41). Using Poisson regression with an assumed two-sided error of 5%, we calculated that a sample size of 226 patients in each group will be needed to detect this reduction with a power of 80%. For the multicenter character of the study, a 20% correction was made, since the variance between the participating centers is unknown. This results in a total sample size of 542, or 271 patients in each group.

Statistical analysis will be performed using SPSS version 21.0 for Windows (SPSS Inc, Chicago, Illinois, United States). The first analysis will be performed by combining the results from the participating centers. After this, the results of the individual centers are analyzed to detect possible differences. The primary analysis consists of a comparison of the primary endpoint (number of complications per patient) between the control group and the EGDT group using Poisson regression. According to secondary endpoints, data will be checked for normal distribution and presented as mean +/-standard deviation when normally distributed, and as median +/-interquartile range when not normally distributed. Relative risks are presented with 95% confidence intervals. Categorical data are tested with Fisher’s exact test. Continuous data are tested with the independent samples t-test when normally distributed, and with the Mann-Whitney U test if not normally distributed. A *P* value <0.05 is considered statistically significant. Analysis will be carried out according to the intention-to-treat principle.

For the quality-of-life assessment, the mean EQ-5D score and the individual SF-36 subscale scores are determined, and a comparison will be made between the standard group and the EGDT group. In addition, mean change scores are determined and evaluated over time. For the economic evaluation, especially the EQ-5D, is of importance as utilities and consequently, quality-adjusted life years (QALY), can be elicited using this generic quality-of-life questionnaire. The incremental cost-effectiveness ratio (ICER) will be expressed as cost differences between groups divided by differences in numbers of serious complications between groups (cost per complication averted). The incremental cost-utility ratio (ICUR) will be expressed as cost differences between groups divided by differences in QALY’s gained between groups (cost per QALY). Confidence intervals will be determined using bootstrapping. A cost-effectiveness acceptability curve will be drawn using this bootstrap sample.

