#### Primary endpoint

The primary outcome measure in this trial is a combined endpoint of major complications in the first 30 days after surgery, including mortality. The use of composite endpoints in trials is common in order to increase statistical power and to capture the net benefit of the intervention [52, 53]. The most important disadvantage of this approach is that interpretation of the results is difficult if the outcomes are of different importance to patients. The components of a composite endpoint should therefore be clearly defined, clinically important, effected by the intervention, as homogeneous as possible, and weighed to reflect their relative importance [53].

The major complications embedded in the composite endpoint in our study are clearly defined and associated with increased long-term morbidity and mortality. Yet there are differences in terms of clinical consequences for the patient. Therefore, we decided to take the number of complications per patient as a primary endpoint, instead of the number of patients with one or more complications. In this way, the severity of the complication is reflected. For instance, if a patient develops pneumonia, which is treated with antibiotics in the ward, there is only one complication registered. If the patient however needs ICU readmission because of respiratory failure and septic shock, three complications are registered. We will report all complications separately to show if a difference in the primary endpoint is predominantly caused by one or more specific complications. In addition, the complications will be weighed using the Accordion complication severity score [31].

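### The primary Poisson test assumes variance equal to mean for a count that scores linked events from one illness separately; a robust variance should be fixed in advance

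*Protocol article*

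**What the plan says.** Under Statistical analysis and sample size calculation, the protocol states that in one participating center's hospital data "the number of major complications embedded in the composite primary endpoint was 0.58 per patient, and that a Poisson distribution was applicable". It aims for a 30% reduction, from 0.58 to 0.41 complications per patient. With a two-sided 5% error and 80% power it arrives at 226 patients per group, then adds 20% because the variance between centers is unknown, giving 542 in total (271 per group). The primary analysis compares the number of complications per patient "between the control group and the EGDT group using Poisson regression". The section mentions no scale parameter, robust variance or negative binomial model, and gives no observed variance.

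Under Primary endpoint (Methodological aspects), the count is chosen over the proportion of affected patients so that severity is reflected. Pneumonia treated on the ward scores one. "If the patient however needs ICU readmission because of respiratory failure and septic shock, three complications are registered".

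Table 2 lists pneumonia as its own item. It defines respiratory failure as "Any other respiratory complication requiring mechanical ventilation (including non-invasive pressure support ventilation" and prolonged ventilation as "Postoperative mechanical ventilation for more than 24 hours (any cause), including non-invasive pressure support ventilation through a face-mask". Severe sepsis and 30-day mortality are further items.

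**The concern.** A Poisson model sets the variance of a patient's count equal to its mean, which is appropriate when events within a patient occur independently. This endpoint is built so that one clinical course can add several events. Such linkage raises the variance above the mean. A plain Poisson standard error does not see this and comes out too small, so the P value and confidence interval of the single primary test would be too optimistic, in the direction of a false positive claim.

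The support for the Poisson assumption is one statement about one center, without the variance that would let a reader judge it.

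A separate matter of wording concerns the count itself. Read literally, Table 2 and the worked example can give different totals for the same patient, and the Trial design and Blinding sections say that outcome assessment is unblinded.

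**Working it through.** **Inputs from the protocol.** Control rate 0.58; 30% reduction, so rate ratio 0.70 and intervention rate 0.406 (printed as 0.41); two-sided 5%; 80% power; 1:1 allocation; 226 per group before and 271 per group after the 20% correction.

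**Input not in the protocol.** The dispersion φ = variance/mean. Assumed range: 1.0 to 2.0.

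**1. The plan's own figure.** The standard formula for Poisson regression with a binary covariate (Signorini), with φ = 1, gives the total

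N = [1.960·√(1/0.25) + 0.842·√(1/0.5 + (1/0.70)/0.5)]² / (0.58·(ln 0.70)²)

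= [3.920 + 0.842·2.204]² / (0.58·0.1272) = 33.35 / 0.0738 = 451.96,

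that is 225.98, or 226, per group. Then 2 × 226 × 1.2 = 542.4, or 542. The stated figures reproduce to the patient, with variance equal to mean. With the rounded rate 0.41 the same formula gives 239, so the exact 30% reduction was evidently used.

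**2. Type I error of a plain Poisson test.** If the true variance is φ times the mean, the nominal z statistic has standard deviation √φ, so the true error is 2·(1 − Φ(1.960/√φ)).

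**3. Power with a valid standard error, 271 per group** (Wald test on the log rate ratio). At φ = 1 the standard error is √[(1/0.58 + 1/0.406)/271] = √(4.187/271) = 0.1243, and 0.3567/0.1243 = 2.869. Power is Φ(2.869/√φ − 1.960).

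| φ | Type I error, plain Poisson | Power, valid standard error | 226·φ per group, before the 20% |
|---|---|---|---|
| 1.0 | 5.0% | 82% | 226 |
| 1.25 | 8.0% | 73% | 283 |
| 1.5 | 11.0% | 65% | 339 |
| 2.0 | 16.6% | 53% | 452 |

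The Wald formula is slightly stricter than the one in step 1: at 226 per group and φ = 1 it gives 75% rather than 80%.

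**4. How much linkage would produce such φ?** Simulation with 14 components, each counted at most once, overall mean 0.58 and 271 per group. A stated share of patients with any complication receives two linked further ones.

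| Share with two linked events | φ | Plain Poisson | Robust variance |
|---|---|---|---|
| 0% | 0.96 | 4.5% | 4.9% |
| 5% | 1.14 | 6.6% | 5.1% |
| 10% | 1.30 | 8.4% | 5.0% |
| 20% | 1.58 | 11.6% | 4.8% |
| 30% | 1.79 | 14.3% | 4.9% |

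The inflation comes from the linkage, and a robust variance removes it.

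**5. Role of the 20% correction.** It multiplies n by 1.2, so for power it offsets φ = 1.2 at most, provided nothing else uses it up. It does not change the standard error formula. At φ = 1.2 a plain Poisson test still has a type I error of 2·(1 − Φ(1.960/√1.2)) = 7.4%.

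**6. The count for one patient.** Take pneumonia that leads to ventilation and septic shock. If respiratory failure in Table 2 covers only complications other than those already listed, the total is two (pneumonia, severe sepsis). The worked example gives three. If ventilation lasts more than 24 hours, the any-cause item could make it four.

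**The case against.** The strongest reply is that the protocol checked the assumption. The center's data concerned the composite itself, so any clustering among its components was present in the data found to fit a Poisson distribution. Some multiple counting also fits a Poisson model: at mean 0.58, 44% of patients are affected, with 0.58/0.44 = 1.32 events each. This stands, and it makes the concern conditional. It does not settle it, because the variance is not shown and the check comes from one center.

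Second, the text names a regression model but no variance estimator, and an analysis plan that is not shown could specify a robust one. This also stands. Plain model-based errors are the natural reading of an unqualified Poisson regression and match the sample size, but the protocol does not say so outright.

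Third, a reader might infer that pooling several centers and types of surgery, with different complication rates, inflates the error further. The documents do not support this, because the Randomization section stratifies by both factors and rate differences between strata are balanced across the groups. With four equal strata with rates from 0.2 to 1.12 (mean 0.58, pooled variance/mean 1.20), simulated plain Poisson tests rejected in about 5% of trials under stratified allocation. They rejected in 7.1% only when strata fell at random in each group.

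Fourth, the respiratory failure item can be read as an event beyond the pneumonia diagnosis, which makes the worked example consistent with Table 2. That reading is possible, so the point is an ambiguity and not a proven contradiction.

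**Conclusion.** The point holds in conditional form. The primary test and the sample size rest on variance equal to mean, while the counting rule gives a concrete reason to expect clustering within patients. Over an assumed φ of 1.25 to 2.0, a plain Poisson test would have a type I error of about 8% to 17%, and honest power at 271 per group would be about 73% to 53%. At φ = 1 there is no inflation and power is 82%.

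A reader might infer that the trial's error rate is inflated by a known amount. The documents do not support that: they report no dispersion, and their one statement on the distribution favors the Poisson model. What they support is that the primary inference should not depend on an undocumented assumption that is nearly free to relax.

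The counting ambiguity is a question of endpoint definition. A reader might take it as a further source of type I error, but nothing in the documents shows that it favors either group. It matters because the Blinding section relies on strict criteria as the safeguard for unblinded assessment.

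**What to change.** 1. Keep Poisson regression and the rate ratio. State, before the outcome data are analyzed, that the primary P value and confidence interval use a robust (sandwich) variance.
2. Report the observed variance/mean ratio by group and, if available, the ratio in the center data behind the figure of 0.58.
3. Separately, reconcile Table 2 with the worked example through one stated rule on whether a ventilation episode in a patient with pneumonia is registered again, and apply it to all patients.

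**Cost.** A model option and a few sentences. If counts are Poisson, there is practically no loss; if they are overdispersed, the interval is wider but correct. One side effect: without stratum terms, a robust variance also absorbs rate differences between strata, which makes it somewhat conservative. In the stratified example above, the error would be about 2·(1 − Φ(1.960·√1.2)) = 3.2%. Including center and type of surgery in the model avoids most of this. The robust variance protects the error rate but does not restore power: if φ proves well above 1.2, 271 per group falls short of 80%.
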